### Outcome measures

The outcome measures are based on the stool diary. The participants complete a stool diary, which is checked by outcome assessors and finally recorded in the Remote Data Capture (RDC) system. The contents of the stool diary include SBMs within 24 hours, straining degree, complete evacuation, stool consistency, use of drugs, etc. Participants will be asked to finish the diaries every day during the baseline assessment period, week 1–8, 11–12, 15–16, 19–20 and 31–32.

This trial includes one primary outcome measure and 8 secondary outcome measures. The primary outcome is the proportion of patients having ≥3 SCBMs/week, averaged over week 3–8. The secondary outcome measures are presented in Table 1. The safety of EA will be evaluated based on various events, including fainting, severe pain, haematoma, local infection, and any feeling of discomfort. The side effects of prucalopride include diarrhoea, nausea, abdominal pain, headache, palpitation, myocardial ischemia (presented in ECG), etc. Any adverse event resulting from EA or adverse drug reaction will be recorded.

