**Table 1 Tab1:** **Secondary outcome measures**

No.	Outcome measure	Time frame	Statistics
1	Proportion of patients having ≥3 SCBMs/week	Week 1–2, week 9–12, week 9–16, week 9–20, week 9-32	CMH test
2	Proportion of patients with one or more increase in SCBMs/week from baseline	Week 1–2, week 3–8, week 9–12, week 9–16, week 9–20, week 9-32	CMH test
3	SCBMs/week and change from baseline	Week 1–2, week 3–8, week 9–12, week 9–16, week 9–20, week 9-32	Nonparametric test
4	SBMs/week and change from baseline in SCBM/week	Week 1–2, week 3–8, week 9–12, week 9–16, week9-20, week 9-32	Nonparametric test
5	Mean Bristol Stool Scale and change from baseline	Baseline, week 1–2, week 3-8	Nonparametric test
6	Straining degree	Week 1–2, week 3–8, week 9–12, week 9–16, week 9–20, week 9-32	Nonparametric test
7	Time to first SCBM	Time from the first treatment to the first SCBM	Nonparametric test
8	Patient assessment of Constipation Quality Of Life (PAC-QOL)	Baseline, week 1–4, week 5-8	*t* test or Mann–Whitney *U* test

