### Sample size and statistical analysis

The sample size will be based on the primary outcome (the proportion of patients having ≥3 SCBMs/week averaged over week 3–8). According to our pilot trial and the literature [4], the proportion of participant having ≥3 SCBMs averaged over week 3–8 was 31.6% for the EA group and 30.9% for the prucalopride group. The figure for the placebo group was 12.0% [4]. Thus, a non-inferiority margin of 10% is reasonable. To assess the non-inferiority between the treatment and control groups, a sample size of 276 for each group will be sufficient, with a one-sided 5% level of significance, a power of 80% and allowing for a 20% dropout. In this trial, we aim to recruit 560 participants, 40 for each hospital.

The data from the 14 centres will be pooled, and the Clinical Evaluation Centre of the China Academy of Chinese Medical Sciences in Beijing will conduct the statistical analysis using the SAS 9.1.3 (SAS Institute, Cary, NC, US) and SPSS Ver.13.0 (SPSS Inc., Chicago, IL, USA) software. The data analysis is based on the intention-to-treat (ITT) population. All statistical analyses will be two-sided tests except for the primary outcome. The level of significance will be established at 0.05. Continuous data will be represented by the mean, standard deviation, median, minimum value, and maximum value; categorical data will be represented by percentages. To compare two independent samples, a t-test or nonparametric test will be used for continuous data, and a chi-square test/the Fisher exact test/nonparametric tests will be used for categorical data. For the primary outcome, the CMH test will be used to avoid the centre effect. The analysis methods for secondary outcomes are presented in Table 1. For safety analysis, the incidence of adverse events will be compared between the two groups using the chi-square test or the Fisher exact test.

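### Table 1 item 4 names the wrong change variable, and the continuous secondary outcomes are tested without the collected baseline value or centre: valid, but less precise than they could be

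*Protocol article*

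**What the plan says.** Under Sample size and statistical analysis, the general rule is "To compare two independent samples, a t-test or nonparametric test will be used for continuous data". The section then sends the reader to the table: "The analysis methods for secondary outcomes are presented in Table 1". Table 1 gives an unspecified nonparametric test for items 3-7 and a t test or Mann-Whitney U test for item 8 (PAC-QOL). No row for a continuous outcome names a covariate or a stratum.

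The same section treats centre differently for the binary primary outcome: "For the primary outcome, the CMH test will be used to avoid the centre effect". Table 1 also assigns CMH to the two binary secondary outcomes, items 1 and 2.

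Baseline values are collected. Under Outcome measures, "Participants will be asked to finish the diaries every day during the baseline assessment period", and the diary covers bowel movements, completeness, straining and consistency. Table 1 lists a baseline PAC-QOL.

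Item 3 of Table 1 reads "SCBMs/week and change from baseline" and item 5 reads "Mean Bristol Stool Scale and change from baseline". Item 4 reads "SBMs/week and change from baseline in SCBM/week".

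**The concern.** There are two separate matters.

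The first is a definition. Item 4 concerns SBMs, but its change score is stated for SCBMs. An analyst who followed the table literally would analyse change in SCBMs twice. Analysing change in SBMs would then be a departure from the published table.

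The second is an analysis choice. A two-sample test of raw follow-up values makes no use of baseline. A test of change scores subtracts the whole baseline value, which over-corrects when baseline predicts outcome only weakly. Neither uses centre, although the plan regards centre as worth handling for the binary outcomes from the same 14 hospitals. Items 3-6 and 8 are five of the eight secondary outcomes, and items 3, 4 and 6 extend to week 32, where the question of a lasting effect lies. Precision on these items is worth having if it costs nothing.

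**Working it through.** **The plan's own figure.** The only computed figure is 276 per group for the primary outcome. With an unpooled variance, control 0.309, EA 0.3167 (the pilot figure in Background), margin 0.10, one-sided 5% and 80% power:

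n = (1.645 + 0.842)² × (0.3167×0.6833 + 0.309×0.691) / (0.10 + 0.0077)² = 230 after rounding up, and 230 × 1.2 = 276.

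It reproduces. Nothing below depends on it, and the protocol gives no calculation for the continuous outcomes.

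**Item 4 against item 3.**

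| Item | Level | Change | Windows |
|---|---|---|---|
| 3 | SCBMs/week | SCBMs/week | weeks 1-2, 3-8, 9-12, 9-16, 9-20, 9-32 |
| 4 | SBMs/week | SCBMs/week | the same six |

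The change parts are identical, with the same windows and the same type of test. No other item lists change in SBMs/week.

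**Precision, equal variances.** Let ρ be the correlation between baseline and outcome. It is not in the protocol, so 0.3-0.7 is an assumption. Taking the variance of a raw follow-up comparison as 1, a change-score comparison has 2(1 − ρ) and ANCOVA has 1 − ρ².

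| ρ | Raw | Change | ANCOVA | ANCOVA vs raw | ANCOVA vs change |
|---|---|---|---|---|---|
| 0.3 | 1 | 1.40 | 0.91 | 9% lower | 35% lower |
| 0.5 | 1 | 1.00 | 0.75 | 25% lower | 25% lower |
| 0.7 | 1 | 0.60 | 0.51 | 49% lower | 15% lower |

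In power terms, assume 280 per arm (560 split 1:1), two-sided 5%, and an effect of 0.237 SD, which a raw comparison detects with 80% power. ANCOVA then has 83.6%, 89.9% and 97.5% at ρ = 0.3, 0.5 and 0.7. Change scores have 65.8%, 80.0% and 95.1%.

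**Precision for bowel-movement counts.** Equal variances are doubtful here. The inclusion criteria hold baseline to two or fewer SCBMs, and two or fewer SBMs per week, while follow-up is uncapped and about 31% are expected to reach three or more SCBMs per week. If k is the ratio of baseline SD to follow-up SD, the relative change-score variance is 1 + k² − 2kρ. ANCOVA remains 1 − ρ². With k assumed at 0.3-0.5:

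- ρ = 0.3, k = 0.3: change 1 + 0.09 − 0.18 = 0.91; ANCOVA 0.91; gain 0%.
- ρ = 0.3, k = 0.5: change 1 + 0.25 − 0.30 = 0.95; ANCOVA 0.91; gain 1 − 0.91/0.95 = 4%.
- ρ = 0.2, k = 0.3: change 1 + 0.09 − 0.12 = 0.97; ANCOVA 0.96; gain 1%.
- ρ = 0.2, k = 0.5: change 1 + 0.25 − 0.20 = 1.05; ANCOVA 0.96; gain 9%.

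Against raw values the gain is 9% at ρ = 0.3 and 4% at ρ = 0.2, whatever k is. A restricted baseline range probably pushes ρ towards the lower values.

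**Centre.** Adjusting for centre lowers variance by roughly the share that lies between centres. For an assumed intraclass correlation of 0.01-0.10 that is 1-10%.

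All these formulas are for comparisons of means. For rank tests they indicate direction and rough size only.

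**The case against.** The strongest reply is that unadjusted two-sample tests are a legitimate choice in a randomised trial, that these outcomes are secondary, and that the non-inferiority conclusion and sample size rest on the primary outcome alone. That stands. A reader might infer that the tests are biased or that the trial's conclusion is at risk, and the protocol supports neither. Chance imbalance is also a modest worry: with 280 per arm the SD of a baseline difference is √(2/280), about 0.08 SD.

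It can also be said that the nonparametric test in items 3-7 is not identified, so a centre-stratified rank test is not ruled out, and that details of adjustment are often left to an analysis plan. This stands in part. A reader should not conclude that centre has been positively excluded for items 3-6. But the general rule describes a comparison of two independent samples, item 8 names two unadjusted tests, and centre is mentioned only in connection with CMH. Read as written, the protocol points to unadjusted tests.

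The third reply is that the largest figure, 35% against change scores, needs equal variances and so cannot be carried over to SBM and SCBM counts. That is right, and the conclusion is limited accordingly.

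On item 4, the objection is that this is a slip whose intended meaning is plain. That is probably so. A reader might infer that the effect on SBMs goes unanalysed, but SBMs/week is still compared in all six windows and only its change score is unlisted. The row nevertheless defines an outcome, and it is wrong as printed.

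**Conclusion.** The point holds as one definite correction and one improvement in precision.

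Item 4 names the wrong change variable, duplicates item 3 and leaves change in SBMs/week unlisted. This needs no assumption.

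Items 3-6 and 8 are assigned valid tests that, as written, use neither baseline adjustment nor centre. The cost is precision, and its size cannot be fixed from the protocol. The 9-49% and 35-15% ranges rest on ρ of 0.3-0.7, equal variances and comparisons of means. They are most plausible for PAC-QOL, Bristol score and straining, which the entry cap does not directly restrict. For SBM and SCBM counts, with ρ of 0.2-0.3 and k of 0.3-0.5 assumed, the gain is 0-9% against change scores and 4-9% against raw values, so it may be only a few percent. Item 7, time to first SCBM, has no baseline value and lies outside the point. The primary analysis is not affected.

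**What to change.** 1. In Table 1, change item 4 to SBMs/week and change from baseline in SBMs/week.
2. For items 3-6 and 8, specify an analysis of the follow-up value by arm, adjusted for the baseline value of the same variable and for centre. Use ANCOVA where the scale allows it. For skewed counts and graded scores, use a rank-based analysis that takes account of baseline and is stratified by centre. Name the method for each row in place of the generic nonparametric test.
3. Report an adjusted difference with a 95% CI for each of these outcomes.
4. Leave item 7 as a separate analysis without a baseline term.

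The cost is wording in Table 1 and the statistical section, or in the analysis plan. The diary and PAC-QOL already supply every variable, and the sample size is unchanged. Trial status reports nineteen participants recruited, so the change can be made well before any analysis.

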## Methods/design

### Study design

This study is a prospective randomised controlled trial. It will be conducted from April 2014 to August 2015 at 14 hospitals around China^a^. Five hundred and sixty participants are planned to be recruited via advertisements in newspapers, television, websites and posters. After being diagnosed by physicians of the gastroenterology or anorectal departments, participants will receive a 2-week long assessment (the stool diary). Randomisation will be performed centrally by the Clinical Evaluation Centre of the China Academy of Chinese Medical Sciences in Beijing, and eligible participants will be randomised into the EA group or the control group. After the baseline assessment has been carried out and the informed consent has been obtained, a randomisation number will be sent to the acupuncturist by phone or online. The statisticians, outcome assessors, and physicians will be blinded to the allocation. The flowchart of the trial is presented in Figure 1. The duration of the trial is 34 weeks, including a 2-week long baseline assessment period (week-2-0), 8-week long treatment period (week 1–8), and 24-week long follow-up period (week 9–32). The time frame of the trial is presented in Figure 2. The trial protocol is in accordance with the principles of the Declaration of Helsinki and has been approved by the review board and ethics committee of the participating hospitals.

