**The flowchart.**

**Figure 2 Fig2:**

**Time Frame of the Trial.**

### Participants

Five hundred and sixty participants met the Rome III criteria [12] are planned to be recruited.

Inclusion criteria: 1) Primary chronic constipation meeting the Rome III criteria, with ≤2 SCBMs (SCBM refers to the feeling of complete evacuation after a bowel movement without the help of drug or hands in the past 24 hours. Bowel movement beyond 24 hours after the use of medicine/hands also could be considered a SCBM). They should conform to at least one of the following items at the same time: a. a feeling of straining during evacuation (at least once per 4 bowel movements); b. lumpy or hard stools (at least once per 4 bowel movements); c. a feeling of incomplete evacuation after a bowel movement (at least once per 4 bowel movements); d. a feeling of obstruction in the anus/rectum (at least once per 4 bowel movements); e. needing the help of hands for evacuation (at least once per 4 bowel movements). 2) Participants who do not meet the diagnosis of irritable bowel syndrome (IBS). 3) Previous laxative use failed to provide satisfactory relief. 4) Patients aged 18 to 75 years old. 5) Two or fewer SBMs per week during the 2-week long baseline assessment. 6) No use of medicine for constipation during the 2 weeks before enrolment (except rescue medication usage); no acupuncture treatment for constipation in the previous 1 month; no participation in any other on-going trial. 7) Volunteered to join this trial and signed the informed consent.

Exclusion criteria: 1) Irritable bowel syndrome, organic constipation or secondary constipation caused by endocrine, metabolic, nervous, postoperative diseases, or drugs; 2) More than one mushy or watery stool during baseline while not taking laxatives (Bristol stool type 6 or 7); 3) A history of pelvic floor dysfunction; 4) Taking medicine that can influence the intestinal function or induce constipation; 5) Severe haemorrhoid or anal fissure; 6) Patients with severe cardiovascular, hepatic or renal diseases, cognitive impairment, abdominal aortic aneurysm or hepatosplenomegaly, aphasia, mental disorders, or illness that will influence the examination or treatment; 7) Women in the gestation or lactation period; 8) Patients with blood coagulation disorders or taking anticoagulants regularly, such as Warfarin and Heparin; 9) Patients with a cardiac pacemaker carrier.

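### The centre-stratified primary responder analysis is valid but does not adjust for the recorded baseline SCBM rate; adjusting may add about 0 to 4 points of power at almost no cost

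*Protocol article*

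**What the plan says.** **Primary analysis.** Under Sample size and statistical analysis: "For the primary outcome, the CMH test will be used to avoid the centre effect". No other covariate or stratum is named for the primary outcome.

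**Endpoint.** Under Outcome measures: "The primary outcome is the proportion of patients having ≥3 SCBMs/week, averaged over week 3–8". It is a yes/no cut of a diary count.

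**Baseline data.** Under Study design, "participants will receive a 2-week long assessment (the stool diary" before a randomisation number is issued. Outcome measures adds: "Participants will be asked to finish the diaries every day during the baseline assessment period". The diary covers spontaneous movements, completeness of evacuation and drug use, so baseline SCBMs/week can be derived for everyone.

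**Entry limits.** Under Participants, the first inclusion criterion caps SCBMs at 2, and the fifth reads: "Two or fewer SBMs per week during the 2-week long baseline assessment".

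**Other responder outcomes.** Table 1 items 1 and 2 also use the CMH test. Item 2 is "Proportion of patients with one or more increase in SCBMs/week from baseline", so baseline enters its definition, but it is not listed as an adjustment.

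**Design inputs.** The expected response "was 31.6% for the EA group and 30.9% for the prucalopride group", and "a non-inferiority margin of 10% is reasonable". The calculation uses a one-sided 5% level, 80% power and a 20% dropout allowance. It gives 276 per group, with 560 to be recruited in total.

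**The concern.** Participants may enter with anything from 0 to 2 SCBMs/week. Someone at 0 needs a rise of 3 per week to count as a responder, and someone at 2 needs a rise of 1. If response depends on the starting value, part of the variation in the primary outcome could be predicted from data already in hand. A centre-only analysis leaves that part in the error.

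The trial's conclusion depends on one interval for the EA minus prucalopride difference, read against 10 points. A prognostic baseline in the model narrows that interval without further patients or visits. It also takes out the part of any chance imbalance in baseline severity that bears on response. The possible loss from omitting it is efficiency; validity is not in question.

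**Working it through.** **Inputs from the protocol article.** Response 0.316 (EA) and 0.309 (prucalopride); margin 0.10; one-sided 5% (z = 1.645); power 80% (z = 0.842); 560 recruited, taken as 280 per arm; 20% dropout.

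**Input the article does not give.** R², the share of variance in the responder outcome explained by baseline SCBMs/week. It is treated as an assumption over a range.

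**Step 1. The plan's own figure.** The sum of the binomial variances is 0.316 × 0.684 + 0.309 × 0.691 = 0.2161 + 0.2135 = 0.4297. The distance from the expected difference to the margin is 0.007 + 0.10 = 0.107.

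n per group = 0.4297 × (1.645 + 0.842)² / 0.107², which rounds up to 233.

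233 × 1.2 = 280, close to the stated 276. With the Farrington–Manning variance the figures are 231.5 and 278. The stated size is thus reproduced approximately from an unadjusted calculation, with no gain from adjustment built in.

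**Step 2. Unadjusted power.** Power = Φ(0.107/SE − 1.645), with SE² = 0.4297/n.

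- n = 224 (280 less 20%): SE = 0.0438, power = Φ(0.798) = 78.8%.
- n = 280 (everyone analysed): SE = 0.0392, power = Φ(1.087) = 86.1%.

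**Step 3. Adjusted power.** Multiply SE² by (1 − R²).

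| R² (assumed) | SE reduction | Power, n = 224 | Power, n = 280 | Evaluable n per group for 80% |
|---|---|---|---|---|
| 0 | 0 | 78.8% | 86.1% | 233 |
| 0.02 | 1.0% | 79.5% | 86.7% | 228 |
| 0.05 | 2.5% | 80.6% | 87.7% | 221 |
| 0.10 | 5.1% | 82.4% | 89.2% | 209 |

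From R² 0.02 to 0.10 the gain runs from 0.7 to 3.6 points at 224 per arm, and from 0.6 to 3.0 points at 280.

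**Step 4. Which R² is plausible.** SCBMs are a subset of SBMs, so the fifth inclusion criterion alone holds baseline SCBMs to 0–2 per week. A simulation (4,000 trials per setting, 224 per arm, baseline 0 to 2 in steps of 0.5, either skewed to low values or uniform, no centre effects) relates the odds ratio per 1 SCBM/week to R² and to the power gain:

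| Odds ratio (assumed) | R² | Power gain |
|---|---|---|
| 1.25 | about 0.005 | about 0 |
| 1.5 | about 0.017 | about 0.6 points |
| 2 | about 0.05 | about 1.3 points |
| 3 | 0.11–0.12 | about 4 points |

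**Step 5. Does the gain survive 14 centre terms?** One simulation used 14 centres of 16 per arm, an assumed between-centre SD of 0.5 on the logit scale and 1,500 trials per setting. It compared the standardised logistic estimate with a centre-balanced difference. Variance ratios were 1.008, 0.981, 0.964 and 0.892 at odds ratios of 1.25, 1.5, 2 and 3. Power changed by about −0.3, +0.7, +1.3 and +3.7 points. A separate 14-centre simulation gave ratios of about 0.99 at odds ratios of 1.25 to 1.5, and about 0.91 to 0.96 at 2 to 3. There is no material loss when baseline is weakly prognostic and a modest gain when it is strong.

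**The case against.** **The size of the gain is unknown and may be nil.** This stands. No correlation or prognostic strength is given, and a baseline confined to 0–2, perhaps with many participants near 0, can explain only so much. At odds ratios of 1.25 to 1.5 the effect is hard to tell from zero.

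**Larger gains.** A reader might assume a baseline–outcome correlation of 0.5 (R² 0.25), which would give 88.0% power at 224 per arm, a gain of 9.2 points. The entry limits make that implausible: an odds ratio of 3 per SCBM/week reaches only about R² 0.12. Even a 5-point gain needs a correlation of about 0.37 (R² about 0.14).

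**Power may already be adequate.** This stands in part. The analysis is stated to be by intention to treat. If all 280 per arm are analysed, unadjusted power is 86.1%. The 78.8% at 224 per arm follows from how dropout was allowed for, which is a separate matter.

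**Bias.** A reader might infer that omitting baseline biases the comparison, or that chance imbalance undermines it. Neither follows. Randomisation and the test's error rate already allow for chance imbalance, and the lack of blinding has no bearing on it.

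**Table 1.** A reader might say that all the responder outcomes ignore baseline. Item 2 does not, since it is defined by change from baseline. Only covariate adjustment is absent there.

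**Covariates belong in the analysis plan.** This carries less weight here. The article does not leave the primary method open: it names the test and the purpose of its one adjustment. A fuller analysis plan might still add baseline, and if so the point is met.

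**Conclusion.** The point holds as a modest efficiency improvement. The centre-stratified analysis is valid, but it leaves unused a baseline that every participant records and that is the same quantity the endpoint dichotomises.

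The plausible gain is about 0 to 4 points of power. It rests on three assumptions: the plan's response rates and margin; 224 evaluable per arm (somewhat less gain at 280); and an R² of no more than about 0.12, which the document neither gives nor excludes. If baseline is barely prognostic, nothing material is gained or lost. Neither bias nor an invalid sample size is shown. The case for acting is that the cost is very small and that planned power at 224 per arm sits just under the stated 80%.

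**What to change.** Pre-specify for the primary outcome a logistic model with treatment, centre and baseline SCBMs/week as a continuous covariate (mean of the 2-week diary). Standardise it over the trial population to the marginal EA minus prucalopride risk difference, and compare its one-sided 95% lower limit with −10 points. The marginal risk difference is needed because the margin is set on that scale; a conditional odds ratio would not match it.

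Keep the centre-stratified unadjusted risk difference as a supporting analysis. Use the same adjustment for Table 1 items 1 and 2.

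Stratifying by centre and baseline category instead is not advised. With two categories it makes 28 strata, averaging 448/28 = 16 evaluable participants, or about 8 per arm.

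**Cost.** A sentence or two in the analysis section and slightly more programming, with no new data, visits or patients. The downside is a primary estimate that depends on a fitted model, which the supporting analysis checks. The article's Trial status section reports nineteen participants recruited, so at that stage the change could still be specified in advance.

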## Background

Twelve percent of adults have constipation worldwide [1]. In China, the figure is 4%-6% [2, 3]. Severe chronic constipation is defined as two or fewer spontaneous, complete bowel movements (SCBMs) per week, hard stool and a sensation of straining during defecation [4]. Due to their widespread use, laxatives are an available choice for constipated patients. However, a high level of dissatisfaction has been reported for laxatives; specifically, evidence supporting the lasting effect of laxatives is limited [5–7]. A study of PEG3350 showed that 38.4 ± 14.1 days after the cessation of PG3350, 29 of 47 (61.7%) patients needed to take additional constipation treatment interventions [8]. A survey of 744 patients with chronic constipation in Europe showed that almost half were using alternative treatments (homeopathy, massage and acupuncture), and nearly 90% of respondents expressed interests in new therapies [6].

With a history of thousands of years, acupuncture has long been used to treat constipation in China. The systematic review [9] we have published concluded that acupuncture was safe for chronic functional constipation and might improve weekly spontaneous bowel movements (SBMs), the quality of life, and relevant symptoms. However, the evidence was limited by the small sample size and the methodological quality. A pilot study (n = 60) we have finished showed that 31.67% patients had 3 or more weekly SBMs after 8 weeks of treatment. By the third month, 40% patients still had 3 or more weekly SBMs, which reflected the lasting effect (effect post treatment) of acupuncture (to be published).

This report is a protocol of a phase-II trial aiming to evaluate the effect of electroacupuncture (EA) versus prucalopride for severe chronic constipation. The World Gastroenterology Organisation recommends prucalopride for patients for whom previous laxative use failed to provide satisfactory relief [10]. It was also considered effective and safe in a randomised controlled trial conducted in the Asia-Pacific region [11]. Thus, the use of prucalopride as the control drug in this trial is reasonable. The objective is to compare the effect of EA versus prucalopride for severe chronic constipation. We will also observe how many patients will not need additional medicine until the 3^rd^ and 6^th^ month post treatment. The safety and acceptance of EA will be simultaneously evaluated.

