## Discussion

Acupuncture has been used to treat constipation in China for thousands of years. Clinical practice and several trials showed that acupuncture is effective for constipation [13, 14]. However, the effect of acupuncture on severe constipation has not been evaluated. A protocol of EA versus sham acupuncture for severe constipation has been published [15].

This is a study design for a non-inferiority, randomised controlled trial aimed to compare the short-term effect (the 3^rd^ to 8^th^ treatment week) of EA with prucalopride for severe chronic constipation. Acupuncture is a non-toxic, economical intervention with minimal adverse effects [16]. If the efficacy of EA is non-inferior to prucalopride, it may be a reasonable option for patients who do not want to experience the side effects of prucalopride. We also want to observe EA’s lasting effect, i.e., EA’s effect at the 3^rd^ and 6^th^ month post treatment. The EA group will be treated for 8 weeks and the prucalopride group will be treated for 32 weeks. A comparison between the two groups after the 8^th^ week could clarify the lasting and dominant effect of EA.

This trial was limited because the participants and acupuncturists could not be blinded. However, the outcome assessors and statistician will be blinded to the allocation.

In conclusion, the trial will compare the effect of EA to that of prucalopride for severe chronic constipation.

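### The primary analysis is a CMH test of no difference between arms, so as written it cannot test non-inferiority against the 10% margin

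*Protocol article*

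**What the plan says.** All references are to the protocol article.

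- Design (Discussion): "This is a study design for a non-inferiority, randomised controlled trial".
- Endpoint (Outcome measures): "The primary outcome is the proportion of patients having ≥3 SCBMs/week, averaged over week 3–8".
- Margin (Sample size and statistical analysis): "Thus, a non-inferiority margin of 10% is reasonable".
- Sample size (same section): "To assess the non-inferiority between the treatment and control groups, a sample size of 276 for each group will be sufficient". The test level is one-sided 5%, the power 80% and the dropout allowance 20%. The planning proportion "was 31.6% for the EA group and 30.9% for the prucalopride group".
- Primary analysis (same section): "For the primary outcome, the CMH test will be used to avoid the centre effect".

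The same section exempts the primary outcome from two-sided testing, sets the significance level at 0.05 and bases the analysis on the ITT population. The abstract also lists the CMH test. Table 1 names the CMH test, in the same unqualified form, for two secondary proportions that have no margin.

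**The concern.** The sample-size paragraph and the analysis paragraph address different hypotheses. The first needs a test of whether EA is worse than prucalopride by 10 points or more. The second names a test of whether the arms differ at all, stratified by centre. A non-significant CMH result does not show non-inferiority, and a significant one speaks to superiority or inferiority.

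This is the only primary analysis. Followed literally, it leads to one of two outcomes. Either the trial needs a significant result in favour of EA and almost never gets one, or a non-significant p-value is taken as non-inferiority with an error rate well above the planned 5%. With no stated rule, the choice between these readings could also be made after the data are seen.

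**Working it through.** **Inputs.** From the sample-size section: EA 31.6%, prucalopride 30.9%, margin 10 points, one-sided 5%, 80% power, 20% dropout, 560 patients at 14 hospitals. Equal allocation gives 280 per arm (20 per arm per centre). Less 20% dropout, this is 224 per arm (16 per arm per centre).

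**1. Reproduce the plan's figure.** The margin-based formula is

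n = (z₀.₉₅ + z₀.₈₀)² × [p_E(1−p_E) + p_P(1−p_P)] / (margin + p_E − p_P)²

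- With 31.6% and 30.9%: 6.183 × 0.4297 / 0.107² = 232.02, rounded up to 233. Then 233 × 1.2 = 280 after rounding up.
- With the pilot figure to two decimals in the Background ("31.67% patients had 3 or more weekly SBMs after 8 weeks of treatment"): 230, and 230 × 1.2 = 276, exactly the stated figure. That pilot figure is for SBMs; it is used here only to retrace the arithmetic.

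The stated size therefore comes from a test against the margin.

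**2. Size needed for the named test.** With no margin the denominator is 0.007²: 6.183 × 0.4297 / 0.007² ≈ 54,200 per arm for 80% power. The trial was not sized for a test of no difference.

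**3. Power at the planning rates, 224 per arm.** SE = √(0.4297/224) = 0.0438.

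- Against the margin: Φ(0.107/0.0438 − 1.645) ≈ 0.79.
- Against no difference, one-sided in favour of EA: Φ(0.007/0.0438 − 1.645) ≈ 0.07.

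For illustration, suppose both arms show 30.9%. The difference is zero, so a test of no difference finds nothing. Yet the lower one-sided 95% limit is −1.645 × √(2 × 0.309 × 0.691/224) = −0.072, or −7.2 points, which is inside the margin. The named test would miss a clear non-inferiority result.

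**4. Error if a non-significant result is read as non-inferior.** Take EA truly 10 points worse (20.9% v 30.9%), 224 per arm.

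- Null SE = √(2 × 0.259 × 0.741/224) = 0.0414.
- True SE = √((0.209 × 0.791 + 0.309 × 0.691)/224) = 0.0411.
- A one-sided test for EA being worse is non-significant when the observed difference exceeds −1.645 × 0.0414 = −0.0681. Probability: 1 − Φ((0.10 − 0.0681)/0.0411) ≈ 0.22.
- With a two-sided 5% test the cut-off is −1.96 × 0.0414 = −0.0811. Probability: 1 − Φ((0.10 − 0.0811)/0.0411) ≈ 0.32.

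**5. Simulation with centre stratification.** 14 centres, 40,000 runs, equal response rates across centres. With equal arms per centre, the Mantel-Haenszel risk difference is the mean of the centre differences.

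| | 224 per arm | 280 per arm |
|---|---|---|
| 31.6% v 30.9%: one-sided CMH favours EA | 6.7% | 7.1% |
| 31.6% v 30.9%: stratified test against −10 points succeeds | 78.7% | 85.9% |
| 20.9% v 30.9%: one-sided CMH does not show EA worse | 21.9% | 14.3% |
| 20.9% v 30.9%: two-sided CMH not significant | 32.4% | 22.9% |
| 20.9% v 30.9%: stratified test against −10 points succeeds (type I error) | 5.1% | 4.9% |

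The simulation agrees with the formulas.

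**The case against.** The strongest reply is that the intent is plain. The margin, the one-sided level and the exemption from two-sided testing sit in the same section as the CMH sentence, and that sentence gives its purpose as handling centre. It could be shorthand for a CMH-weighted risk difference compared with −10 points, which would be valid, with the interval method left to an analysis plan. That may be what was meant, but the article does not say so: it names a test, not an estimator or a limit, and Table 1 uses the same term where no margin exists. One-sidedness does not help either, because it fixes the direction of the alternative and leaves the null at no difference. Nor is this a detail left open, since the article fixes a specific method that does not match its hypothesis.

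Four narrower points stand and limit the illustration:

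- A significant one-sided CMH result in favour of EA would imply non-inferiority, but it occurs in only about 7% of trials at the planning rates.
- The inflated error rates are conditional on reading non-significance as non-inferiority, which the article nowhere states as its rule.
- The two-sided figures lie outside the plan's one-sided rule for the primary outcome, so the one-sided figures are the relevant ones.
- The analysis is ITT, so 280 per arm is as relevant as 224. Both are shown.

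**Conclusion.** The concern holds and must be fixed. The named primary test does not address the non-inferiority hypothesis for which the trial was sized. Taken literally, it gives about 7% power at the planning rates, where a margin-based stratified test gives about 79% (224 per arm) to 86% (280 per arm). If a CMH result that does not show EA worse were read as non-inferior, the error at a true 10-point deficit would be about 14% (280 per arm) to 22% (224 per arm) against the planned 5%.

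These sizes assume that the margin is on the risk-difference scale, allocation is equal, centres are of equal size and response rates are the same across centres. The mismatch itself depends on none of the last three.

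**What to change.** Replace the CMH sentence for the primary outcome with wording such as:

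> The primary analysis is the centre-stratified Mantel-Haenszel risk difference (EA minus prucalopride) in the proportion of patients with ≥3 SCBMs/week averaged over weeks 3–8. Non-inferiority is concluded if the lower one-sided 95% confidence limit (the lower bound of the two-sided 90% interval) is above −10 percentage points.

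Align the mention of the CMH test in the abstract. Another stratified method that compares a confidence limit with the margin would also serve. The CMH test may be kept as an optional superiority test once non-inferiority is shown; the fix does not depend on it.

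The cost is one sentence of analysis wording. Centre adjustment is kept, the alpha is the stated one, and the planned size already fits. The article's trial status gives nineteen participants recruited, so at that point the rule could still be set well before any results.
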